#### Intervention arm core clinic components

Overarching strategies are outlined in Table 2. Once the clinic is assigned to the intervention arm, they will be asked to designate two clinic champions per clinic including one physician or advanced practice provider (APP) and one person who would manage daily workflows such as a practice manager or senior medical assistant. These individuals will complete a survey on organizational readiness to change [28]. Champions will also answer basic questions about workflow related to CRC screening. Within the first month of rolling out the program at a new clinic the patient navigators and study team members will schedule a site visit to review project goals including cultural tailoring and relevance for Black and Hispanic/Latino populations, provide provider and patient facing materials about the navigation program, and complete any baseline clinic level assessments that may affect how the navigation program is delivered. Providers will be asked to refer Black and Hispanic/Latino patients age 45 to 75 years old who have previously missed screening or require assistance to complete screening due to transportation, stigma, health literacy, or other barriers.

**Table 2 Tab2:** Example implementation strategies

Strategy category	Individual strategy	Study application
Evaluative and iterative	Assess for readiness and identify barriers and facilitators	Clinic level assessments upon joining the intervention arm
	Audit and provide feedback	Utilize internal dashboard to provide regular updates on CRC screening by race/ethnicity to providers within intervention clinics
Develop stakeholder relationships	Build a coalition	Work with the community advisory board to understand root causes of disparities, review proposed intervention materials, ongoing review to best serve community members
Engage consumers	Intervene with patients to enhance uptake and adherence	Conduct formative interviews with patients and collect ongoing feedback on experiences with intervention; outreach by phone and patient portal
Change infrastructure	Change record systems	Utilize OMOP Common Data Model to define outcome; create referral orders specific to individual primary care sites
Train and educate stakeholders	Conduct educational meetings with stakeholders	Meet with clinical champions including physicians and administrators to review project goals and solicit feedback; engage system leadership

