During the six-month active support period, the study team will review weekly data and will reach out to clinics if two sequential weeks of continuous data during the six-month of active support period show that providers are not referring eligible patients to navigation in order to meet the minimum sample size of 20 patients per clinic per six months. We will meet with the clinical champions first and if needed will conduct additional site visits to troubleshoot, develop additional supportive materials, or consider how communication or reminders through the electronic health record (EHR) might be needed to support referrals to patient navigation. Conversely, it is possible that we will receive too many referrals, whereby it appears that providers are referring everyone due for screening rather than those who have a history of not completing screening or identified barriers to screening. If this is the case, we will consider providing decision support tools for triaging who needs referral or creating a system within our team to stratify intensity of support based on the number of previous referrals/orders that were incomplete or identification of social needs in the medical record.

The research team will review data bi-weekly and communicate with the clinical champions at least monthly during the initial six months in the intervention arm. This data will include progress of CRC patient navigation referrals and completion of screening. After the six-month intensive support, they will receive quarterly updates on CRC screening completion rates overall and by provider, broken down by patient race/ethnicity.

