### Patient navigation- Patient-level component

#### Patient eligibility and initial CRC outreach

Patients will be eligible if they are 45 to 75 years old, identify as Hispanic/Latino and/or Black, are not up to date on CRC screening recommendations, and have had at least one primary care visit at the included clinics in the past 365 days. The target population of patients who are due for screening is intended to align with the quality metrics relevant to CRC screening in the healthcare system. While we are not limiting to annual well visits, we will conduct sensitivity analyses to understand how reason for a visit affects screening referral, navigation referral, or completion outcomes. For clinics in the intervention phase, the provider will have the option to refer patients to navigation. Two days prior to their primary care appointment, patients will receive a reminder via text message indicating that their CRC screening is due and encouraging them to talk to their doctor about CRC screening.

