### Measures and outcomes

#### Primary outcome

Our primary effectiveness outcome is clinic-level CRC screening completion rates every six-months for Black and Hispanic/Latino patients aged 45 to 75 years old comparing intervention and control conditions (within and across clinics). Our grant partner, the National Committee on Quality Assurance (NCQA) will lead translation of the HEDIS® colorectal cancer screening (COL) quality measure from the Fast Healthcare Interoperability Resources data model into the Observational Medical Outcomes Partnership (OMOP) common data model, supporting efficient, reliable, outcome measurement to support translation of findings into policy-aligned practice. This will include development of all existing COL cohort definition in ATLAS, [41] creation of the ATLAS concepts (using the HEDIS Value Set Directory as a primary reference, without external publication or replication of those value sets), and creation of the COL artifacts for implementation in the MedStar Health dataset. Definitions and concepts will undergo iterative review with both NCQA and MedStar Health teams to ensure accuracy and implementation feasibility. These Observational Health Data Sciences and Informatics query definitions can be run at any institution and will be made publicly accessible. All data on completion of CRC screening by race and ethnicity will be extracted from the EHR under a HIPAA waiver. We will also consider intersectional characteristics of participants such as age and payor in addition to race and ethnicity. We will compare EHR data extracted manually to follow quality metric standards with data obtained through the OMOP Common Data Model to cross-validate results.

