The study was powered to detect a significant difference in the CRC screening rates between Black and Hispanic/Latino patients who receive navigation services and those who do not receive navigation. The design consists of 15 clusters and 6 steps (one baseline all clusters in control condition + 5 intervention steps) of six-month duration where 3 clusters will switch to intervention every 6-month. A sample size of an average of 120 participants (60 intervention and 60 control) per cluster and an average of 20 participants per cluster/step will achieve 80% power with 1800 participants (900 navigation and 900 control participants) to detect a conservative 10-percentage point difference in the primary outcome measure of CRC screening completion. The navigation intervention is expected to increase the screening rate from an average 60% (current data across clinics) to an average of 70%. The test statistic used was the two-sided Wald Z-test, the intra-class correlation (ICC within-clinic) was assumed to be 0.05 and the Type I error was 0.05. Sample size calculations were conducted in PASS 15 [50]. Since the navigation will be applied to all referrals and we will obtain screening completion data from EHR, this sample size will be considered as the minimum number of patients to achieve the anticipated effect size.

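### The stated 80% power is for navigated versus non-navigated patients, but the primary outcome compares all due patients by clinic condition, so power for the primary analysis is undetermined

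*Protocol article*

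**What the plan says.** The sample-size paragraph (Protocol article, Data analysis plan) sets the contrast: "The study was powered to detect a significant difference in the CRC screening rates between Black and Hispanic/Latino patients who receive navigation services", as against patients without navigation. On the layout it says: "The design consists of 15 clusters and 6 steps (one baseline all clusters in control condition + 5 intervention steps"), with three clinics crossing over every six months. It then says that "an average of 20 participants per cluster/step will achieve 80% power with 1800 participants (900 navigation and 900 control participants"), for a rise in completion from 60% to 70%, ICC 0.05, two-sided Wald test at 0.05. It calls this sample size a minimum.

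The section Intervention arm core clinic components ties the figure of 20 to referrals. The team contacts a clinic when its providers are not referring eligible patients "in order to meet the minimum sample size of 20 patients per clinic per six months".

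The Primary outcome section defines something else: "Our primary effectiveness outcome is clinic-level CRC screening completion rates every six-months for Black and Hispanic/Latino patients aged 45 to 75 years old", compared between intervention and control conditions. The Data analysis plan takes the patient-level outcome as completion among patients identified as due for screening, with a treatment indicator, step effects and random clinic effects. The Discussion keeps a clinic that stops participating under its randomised assignment, with outcomes taken from the EHR.

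Navigation reaches only some of these patients: "For clinics in the intervention phase, the provider will have the option to refer patients to navigation". Providers are asked to refer those "who have previously missed screening or require assistance to complete screening due to transportation, stigma, health literacy, or other barriers". Referral of everyone due is described as too many referrals. Reach is a secondary outcome, and no value is assumed for it.

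**The concern.** The power calculation and the primary analysis use different populations. In the calculation, all 20 patients in an intervention clinic-step are navigated and carry the full 10 points. In the analysis, an intervention clinic-step contains every due patient, and by design only a selected part of them is navigated. Two quantities decide the power of that analysis: the number of due patients per clinic-step, and the average gain across all of them. The article gives neither.

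At stake is what the 80% assures. A study team could reach 20 referrals in every clinic-step, believe that the power requirement is met, and still have power well away from 80% in either direction for the outcome named as primary.

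**Working it through.** **Inputs from the article.** 15 clinics, 6 periods, 3 clinics crossing per step, 20 patients per clinic-step, 60% versus 70%, ICC 0.05, two-sided alpha 0.05.

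**Inputs assumed.** N, the due patients per clinic-step; f, the fraction of them who are referred and navigated; no gain in non-referred patients, so that the clinic-wide difference is d = f × 0.10.

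**Formula.** Hussey-Hughes variance for a cross-sectional stepped wedge, with v = p(1−p), clinic variance τ² = 0.05v and cell-mean variance s² = 0.95v/N:

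Var = I·s²(s² + Tτ²) / [(IU − W)s² + (U² + ITU − TW − IV)τ²]

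Here I = 15 and T = 6. U = 45 intervention cells. W = 0² + 3² + 6² + 9² + 12² + 15² = 495. V = 3 × (5² + 4² + 3² + 2² + 1²) = 165. Then IU − W = 675 − 495 = 180, and U² + ITU − TW − IV = 2025 + 4050 − 2970 − 2475 = 630. Power = Φ(d/SE − 1.96).

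**The plan's own figure (N = 20, d = 0.10).**
- v = 0.70 × 0.30 = 0.21: SE 0.0360, power 79.3%.
- v = 0.65 × 0.35 = 0.2275: SE 0.0375, power 76.0%.
- v = 0.60 × 0.40 = 0.24: SE 0.0385, power 73.8%.

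So 80% is approached only when every analysed patient carries the full 10 points. The cell count agrees: 45 × 20 = 900 per condition.

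**The primary contrast (v = 0.2275).** The comparable anchor is therefore 76.0%, not 80%. The last column moves one-fifth of the clinic variance to the clinic-by-step level (an assumption): τ² = 0.8 × 0.05v and s² = 0.95v/N + 0.2 × 0.05v.

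| N due | referred | f | d (points) | SE | power | power with clinic-by-step variance |
|---|---|---|---|---|---|---|
| 40 | 20 | 50% | 5.0 | 0.0271 | 45% | 35% |
| 60 | 20 | 33% | 3.3 | 0.0223 | 32% | 22% |
| 100 | 20 | 20% | 2.0 | 0.0174 | 21% | 13% |
| 200 | 20 | 10% | 1.0 | 0.0124 | 12% | 7% |
| 100 | 50 | 50% | 5.0 | 0.0174 | 82% | 53% |
| 200 | 100 | 50% | 5.0 | 0.0124 | 98% | 64% |
| 500 | 125 | 25% | 2.5 | 0.0078 | 89% | 25% |

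The first four rows hold referrals at the stated minimum of 20. The last three let referrals grow with the number due.

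**The same result without a reach assumption.** The clinic-wide difference that gives 80% power is (1.96 + 0.84) × SE. Without clinic-by-step variance it is 7.6 points at N = 40, 4.9 at N = 100, 3.5 at N = 200 and 2.2 at N = 500.

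**The case against.** **A clinic-wide reading exists.** The 60% is described as current data across clinics, rising to an average of 70%, and the same paragraph speaks of 60 intervention and 60 control patients per clinic. Because 45 × 20 = 900, the 900 navigation participants could be a loose label for patients in intervention cells. On that reading 10 points is already the by-condition effect. This cannot be excluded, but the paragraph's opening sentence and the tie between 20 and referrals both contradict it. The text has to be reconciled either way.

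**Twenty is a minimum.** Outcomes come from the EHR, so N may be large, and the article plans for an excess of referrals. This stands. A reader might infer that the trial is badly underpowered. The document does not support that, since some rows of the table exceed 80%.

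**Non-referred patients may also gain.** Intervention clinics receive audit and feedback, provider reminders and educational materials. The article does not say clearly whether the pre-visit text reminder is confined to the intervention phase. The product f × 10 points is therefore an assumption. For illustration, with 100 due and 20 referred, a 3.75-point gain in the other 80 gives 0.20 × 10 + 0.80 × 3.75 = 5 points, and power of 82% instead of 21%.

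**A biased comparison is not planned.** A reader might infer that 900 referred patients will be compared with 900 unreferred controls, which randomisation would not protect. No section plans that as the primary analysis. Nor does it follow that a null result would be misread, because reach, adoption and fidelity are all to be reported.

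**An article may leave counts to the full protocol.** That is fair for the counts. The mismatch between the stated contrast and the stated outcome is in the article's own text.

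**Conclusion.** The concern holds as a mismatch. The 80% is stated for navigated versus non-navigated patients, while the primary outcome compares all due patients by randomised condition, with optional and selective referral of unstated extent. The 80% does not carry over, and power for the primary analysis is undetermined. Under the no-spillover assumption it runs from 12% to 98% over the values of N and f shown, and it is lower wherever clinic variance also varies by step. The figures rest on assumed N and f, a linear approximation on the risk-difference scale, and ICC 0.05. That the primary analysis is by intention to treat is inferred from the outcome definition and the rule for clinics that stop; no single sentence says so for the primary model.

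**What to change.** - State that the primary contrast is the by-condition (intention-to-treat) effect in all eligible due patients, and reword the opening of the sample-size paragraph to match.
- Restate power using the baseline EHR count of due patients per clinic-step, an explicit assumed reach and an explicit assumed clinic-wide effect. Alternatively, state the minimum reach or minimum clinic-wide difference that gives 80% power. Show the result with and without clinic-by-step variance.
- Describe 20 patients per clinic per six months as a referral-monitoring target, not as the sample size for the primary analysis.

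Using crossover as an instrument to recover the effect in navigated patients is not advised here. It requires crossover to act only through navigation, and the clinic-wide components threaten that.

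Cost: one recalculation and some rewording. Clinics are stratified by the number due and the baseline period was used to verify the EHR extraction, so the counts should be obtainable. The stated power may become less favourable. No extra patients are needed.

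### At the stated minimum of 20 patients per clinic-step (1,800 in total), the protocol's own inputs give about 76% power for a 10-point difference, not 80%

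*Protocol article*

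**What the plan says.** The sample-size paragraph closes the Data analysis plan of the protocol article. It sets out the layout: "The design consists of 15 clusters and 6 steps (one baseline all clusters in control condition + 5 intervention steps) of six-month duration". Three clinics cross over at each step after baseline. The size is "an average of 120 participants (60 intervention and 60 control) per cluster and an average of 20 participants per cluster/step", and the claim is that this "will achieve 80% power with 1800 participants (900 navigation and 900 control participants) to detect a conservative 10-percentage point difference in the primary outcome". The intervention is expected to "increase the screening rate from an average 60% (current data across clinics) to an average of 70" per cent. The remaining inputs are a "two-sided Wald Z-test, the intra-class correlation (ICC within-clinic) was assumed to be 0.05 and the Type I error was 0.05". The calculation is attributed to PASS 15, without the variance option or other settings.

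Two further statements bear on the point. The same paragraph treats the sample size as a minimum, because outcomes come from the electronic health record (EHR). The section on the intervention arm's core clinic components uses 20 patients per clinic per six months as the floor that prompts contact with a clinic when referrals lag. The paragraph before the sample-size text specifies fixed step effects and random clinic effects for the primary model.

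**The concern.** The paragraph gives every input that a stepped-wedge power calculation needs except the variance convention, so the 80% can be checked. It does not come back. The 80% is attached to exactly 1,800 patients and 20 per clinic-step, and the trial team monitors against that same 20. If 20 gives less than 80% power, the floor is slightly too low for the purpose the protocol gives it, and readers who rely on the published figure have a somewhat too favourable view of the trial's sensitivity to a 10-point effect.

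**Working it through.** **Inputs (all from the Data analysis plan).** I = 15 clinics; T = 6 periods; three clinics cross at each of periods 2 to 6; n = 20 per clinic-period; rates 0.60 and 0.70; ICC = 0.05; two-sided Z at 0.05. The treatment effect is one constant difference, as in the sample-size paragraph. The variance convention is not stated. I start with the pooled rate 0.65, with the ICC taken as a share of total variance, and then vary this.

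**Step 1: the layout, which reproduces.** Intervention cells: 3 × (5 + 4 + 3 + 2 + 1) = 45 of 15 × 6 = 90. Patients: 90 × 20 = 1,800, of which 45 × 20 = 900 are under intervention and 900 under control. Per clinic this averages 60 and 60. The stated sizes are consistent.

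**Step 2: the power, which does not reproduce.** The Hussey-Hughes variance of the treatment effect is

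Var = I·s²·(s² + T·τ²) / [(I·U − W)·s² + (U² + I·T·U − T·W − I·V)·τ²]

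- U (intervention cells) = 45
- W (sum of squared period totals) = 0 + 9 + 36 + 81 + 144 + 225 = 495
- V (sum of squared clinic totals) = 3 × (25 + 16 + 9 + 4 + 1) = 165
- Total variance = 0.65 × 0.35 = 0.2275
- τ² = 0.05 × 0.2275 = 0.011375
- s² = 0.95 × 0.2275 / 20 = 0.010806
- I·U − W = 675 − 495 = 180
- U² + I·T·U − T·W − I·V = 2,025 + 4,050 − 2,970 − 2,475 = 630

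Numerator: 15 × 0.010806 × (0.010806 + 0.068250) = 0.012814. 
Denominator: 180 × 0.010806 + 630 × 0.011375 = 1.9451 + 7.1663 = 9.1114. 
Var = 0.0014064 and SE = 0.0375.

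Power = Φ(0.10 / 0.0375 − 1.96) = Φ(2.667 − 1.960) = **76.0%**.

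Direct generalised least squares gives the same 76.0%. Simulation of the same linear analysis (4,000 runs) gives 76.3%, and a logistic mixed-model simulation (1,500 runs) gives 75.0%.

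**Step 3: other variance conventions.**

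| Binomial variance used | ICC on total variance | Binomial variance taken as the residual |
|---|---|---|
| 60% rate in every cell (0.24) | 73.8% | 71.6% |
| Pooled rate (0.2275) | 76.0% | 73.9% |
| Average of the two rates (0.225) | 76.5% | 74.3% |
| 70% rate in every cell (0.21) | 79.3% | 77.2% |

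Arm-specific variances give 76.5% and 74.4% in the two columns. On the log-odds scale, arm-specific variances give 73.9% to 76.7%, and the 60%-rate variance in every cell gives 78.6%.

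**Step 4: readings that pass 80%.** Each departs from the text: a one-sided test (81% to 87%), no period effect (98.4%), 0.05 read as a coefficient of variation (84% to 86%), and 24 patients per cell (82.7%).

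**Step 5: what would give 80%.** The detectable difference at n = 20 is (1.960 + 0.842) × 0.0375 = 10.5 points with the pooled variance (10.1 to 10.8 across the first column of the table). Alternatively, with the pooled variance and the ICC on total variance, 22 per clinic-step (22 × 90 = 1,980 patients) gives 79.6% and 23 (2,070 patients) gives 81.2%.

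**The case against.** The strongest reply has three parts.

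- **Twenty is a floor.** The primary analysis takes patients due for screening from the EHR and is not capped at 20 per clinic-step. Two or three more patients per cell close the gap. This stands as a limit on the consequence: power in the completed trial is unknown and may well exceed 80%. It does not rescue the sentence, which ties 80% to 1,800 patients.
- **The variance setting is not shown.** A journal article can leave software settings to the full protocol, and one convention comes within a point of the stated figure. This stands as a reason to ask which setting was used. But that convention applies the 70%-rate variance to control cells assumed to be at 60%, and it still gives 79.3%.
- **The gap is small.** It is about four points of power, or half a percentage point of detectable difference. This stands: the design, the analysis and the validity of the result are untouched.

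A reader might go further and infer that 76% is a best case, because the calculation assumes a clinic effect that is stable over time and a normal reference distribution with 15 clusters. The documents do not support that. The 76% is power at a minimum cell size, and more patients raise it. Allowances for clinic-by-step variation or a small-sample reference would lower it, but the documents give no values for either. Any figure would rest on the reader's own assumptions, and leaving them out is not an arithmetic error. Nor does the calculation bear on whether a 10-point effect is a cautious assumption.

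**Conclusion.** The point holds as a modest arithmetic discrepancy. At 20 patients per clinic-step and 1,800 in total, the stated inputs give about 76% power for 60% versus 70%. The range is about 72% to 79% by variance convention, and no reading faithful to the text reaches 80%. This rests on the standard model with fixed period effects, a single random clinic intercept, equal cells of 20 and a constant treatment effect, which matches the stated inputs. It does not show that the trial is underpowered, since the number analysed may exceed the floor. Nor does it show that the software was misused, since its settings are not reported.

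**What to change.** Retrieve the PASS 15 run and state the variance convention and settings. Then restate the figure: at 1,800 patients, about 76% power for a 10-point difference, or 80% power for a difference of about 10.5 points. If the retrieved settings give another value within the range above, report that value with its convention. Because 20 is a minimum, the text may add that about 22 to 23 patients per clinic-step (about 1,980 to 2,070 in total) would give 80% for 10 points.

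The cost is a sentence or two and a slightly less favourable figure. Restating needs no extra patients and no change to design or analysis.
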